### Analysis of RCT and observational trial

Carrying out this RCT is only justifiable if there is a realistic chance of enrolling enough patients to complete a meaningful statistical analysis. Therefore, an intermediate assessment of the randomized patient population will be performed after the first and second years of recruitment. If the numbers are deemed to be insufficient, additional study sites will be added and a web-based information platform will be launched in the hopes of garnering additional attention from affected patients and physicians.

If less than 5% of patients agreed to randomization within the first year and less than 10% within the second year, the RCT will be stopped and continued solely as an observational trial (see Table 1). Due to the dual study design (parallel RCT and observational cohort), the following analysis scenarios are possible:

**Table 1 T1:** Time Schedule

Start	-> Start of recruitment phase (presumably Sep. 2009)
End of year 1	**->**Intermediate assessment of recruitment level:
	- If fraction of randomized patients <5% of total count: ongoing recruitment, else abortion of randomization

End of year 2	**->**Second intermediate assessment of recruitment level:
	- If fraction of randomized patients <10% of total count: ongoing recruitment, else abortion of randomization

End of year 4	**-> End of recruitment phase**

	-

Year 5+6	**->**Follow-up
Year 7+8	
Year 9	
End of year 9	**-> End of Follow-Up**

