**Methods/Design:**

The present study is a non-blinded, prospective, multi-center randomized controlled trial (RCT). As the primary clinical endpoint, overall-survival in patients receiving postoperative radiation therapy vs. patients without adjuvant therapy following curative intended surgery is compared. The aim of the study is to enroll 560 adult males and females for 1:1 randomization to one of the two treatment arms (irradiation/no irradiation). Since patients with small tumor (T1/T2) but singular lymph node metastasis are rare and the amount of patients consenting to randomization is not predictable in advance, all patients rejecting randomization will be treated as preferred and enrolled in a prospective observational study (comprehensive cohort design) after giving informed consent. This observational part of the trial will be performed with maximum consistency to the treatment and observation protocol of the RCT. Because the impact of patient preference for a certain treatment option is not calculable, parallel design of RCT and observational study may provide a maximum of evidence and efficacy for evaluation of treatment outcome. Secondary clinical endpoints are as follows: incidence and time to tumor relapse (locoregional relapse, lymph node involvement and distant metastatic spread), Quality of life as reported by EORTC (QLQ-C30 with H&N 35 module), and time from operation to orofacial rehabilitation. All tumors represent a homogeneous clinical state and therefore additional investigation of protein expression levels within resection specimen may serve for establishment of surrogate parameters of patient outcome.

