## Background

Ninety percent of all tumors in the head and neck region are of squamous cell origin and world wide annual incidence is estimated at 363.000 with a mortality of 200.000 [1,2]. Oropharyngeal squamous cell carcinoma (OSCC) is the predominant malignancy in the head and neck region, and is the seventh most frequently occurring tumor world-wide. In the Federal Republic of Germany, up to 3-5% of all malignant tumors are found within the oral cavity and the oropharynx, with 7.500 new cases annually. 2.2% cases of death occur as a consequence of oropharyngeal malignancy [3]. Thus, treatment of patients with OSCC is of great medical and economic importance. Prevailing curative therapeutic strategies combine radical resection of the tumor with a safety margin, followed by radiation of the original tumor site and adjacent locoregional lymphatic drainage areas [4-6]. To date, selection of the individual therapeutic pattern is essentially guided by pre- and post-therapeutic TNM staging parameters. Particularly for advanced tumors, postoperative radiotherapy, possibly combined with chemotherapeutic agents, is favorable and recommended [7-9]. Interdisciplinary guidelines state the following detailed recommendations for application of adjuvant radiation therapy:

- non in sano resection if reoperation is impossible (R1-, R2-status)

- primary tumor status > pT2 and pN2, pN3

- extranodular spread of the disease

- lymphangiosis carcinomatosa

- facultative: pN1

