### Randomization and Sample Size

The present study design consists of a two-armed, randomized controlled trial (RCT), but patients who refuse to participate in a randomized approach and who express a radiation preference will be included in a prospective observational study after giving informed consent. This parallel observational trial will follow the same treatment and observation protocol as the RCT. Patients who agree to the randomized trial will be randomized and stratified according to lymph node therapy (yes/no) as formulated by the DOESAK [12]. Randomization to the radiation group and control group will be done 1 to 1, with recruitment extending over a period of 4 years and ongoing, annual follow-up continuing until the trial ends, i.e. for at least 5 years for each patient. Sample size calculation will be performed for the two-sided log rank test at a significance level of 5%. Assuming exponential distributed survival with 45% survival within the control group and 55% within the radiation group after 5 years (as per results observed in the DOESAK collective), and a drop-out rate of 5% per year, 280 patients per group are required to detect a difference of 5% in overall survival with a power of 70%. To ensure proper power adjustment, an intermediate analysis of the true drop out rate will be conducted. Recruitment of at least 280 patients per group in the observational study will be pursued only in the unfortunate event that patient recruitment within the randomized trial fails.

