## Discussion

Randomized (blinded) clinical trials represent the gold standard for comparison of treatment efficacy as postulated by the criteria of modern evidenced based medicine [14]. Therefore, RCTs are desired to establish "Grade A" treatment recommendations. A key advantage of randomization is the equal distribution of known and unknown confounding variables within intervention groups, and the elimination of their influence on the outcome [15]. Only the experimental design of a RCT reduces the otherwise unavoidable risk of selection bias and systematic differences which are not induced by the treatment itself, but may affect the outcome. Thus, the study described in this paper could provide a reliable, unbiased appraisal of radiation effectiveness. However, field experience from studies with strongly differing therapy regimens have shown that randomization might fail due to a strong preference of patient and/or physician for a certain therapeutic option (preference effect) [15-17]. Within the "German Breast Cancer Study Group" (GBSG) which investigated operation vs. radiation, only 6.4% of eligible patients consented to randomization [18,19]. Conducting such a study as RCT might not be suitable as a source of evidence due to essential loss of statistical power. External generalization of such data might be harmful if comparison to the intended target population is not supported by a sufficient patient count. Unfortunately the magnitude of the preference effect can not be estimated in advance, although its occurrence in the present study is highly probable due to similarities to the German Breast Cancer Study Group. Thus, the present study setup also uses a comprehensive cohort design. In the unfortunate event that the study fails as a RCT, the obtained clinical data will still allow careful evaluation of radiation effectiveness under controlled conditions in specialist centers. Furthermore, this valuable clinical data might serve as a useful guide for the design of controlled clinical trials in the future. Using a comprehensive cohort design, Rauschecker et al. enrolled more than 1000 patients within the "German Breast Cancer Study Group" (GBSG), and presented a valuable outcome after a long observational period [19].

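### The rule for stopping the RCT is a consent share (5%, then 10%) that is not linked to the 560 patients who must be randomised

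*Protocol article*

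**What the plan says.** Under Analysis of RCT and observational trial, the protocol article sets its own condition: "Carrying out this RCT is only justifiable if there is a realistic chance of enrolling enough patients to complete a meaningful statistical analysis". From this it derives assessments after the first and second recruitment years. Two actions follow.

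- If numbers are judged insufficient, sites are added and a web platform is launched. No figure is given, and this step does not stop the RCT.
- If fewer than 5% agree to randomisation in year 1 and fewer than 10% in year 2, the RCT stops and the study continues as observational only.

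Table 1 prints the second rule the other way round: below the threshold recruitment goes on, otherwise randomisation is aborted.

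The target is in the abstract ("The aim of the study is to enroll 560 adult males and females for 1:1 randomization") and under Randomization and Sample Size (280 per group, 70% power). The analysis section then gives two scenarios. The randomised arms are compared if a sufficient number were randomised; otherwise all recruited patients are analysed with adjustment. Sufficient has no figure. Outcome measurements fixes the primary analysis as intention to treat on the randomised subjects.

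**The concern.** The condition concerns a number: enough patients for a meaningful analysis. The stop rule measures a proportion. Without an expected total enrolment, which the article does not give, a proportion cannot show whether 560 is reachable. A trial could therefore meet the consent threshold and still be heading for a small fraction of its target.

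The risk is foreseeable on the article's own account. The abstract calls these patients rare, and the Background lists few eligible patients at each centre as a key problem. The Discussion considers a preference effect highly probable and cites a precedent in which "only 6.4% of eligible patients consented to randomization".

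At stake is whether the year-1 and year-2 checks can do the job for which they were introduced. If they cannot, randomisation may continue with little prospect of answering the primary question. The choice between the randomised and the all-patient analysis would then be left to a later judgement without a stated criterion.

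**Working it through.** **Inputs** (all from the protocol article)
- Survival: "Assuming exponential distributed survival with 45% survival within the control group and 55% within the radiation group after 5 years"; two-sided log-rank test at 5% (Randomization and Sample Size).
- Loss: "a drop-out rate of 5% per year" (same section).
- Recruitment over 4 years, follow-up of 5 to 9 years (Follow-Up).
- Incidence: "7.500 new cases annually" in Germany, oral cavity and oropharynx, not limited by stage (Background).
- Assumed here: uniform accrual, exponential dropout, and a consent share counted as randomised over all enrolled, as in Table 1.

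**Step 1: reproduce the plan's sample size.**
- Hazards: −ln(0.45)/5 = 0.1597 and −ln(0.55)/5 = 0.1196, so HR = 0.749. Dropout hazard: −ln(0.95) = 0.0513.
- Event probability per arm, with t = λ + δ: (λ/t) × [1 − (e^(−5t) − e^(−9t))/(4t)]. This averages 0.531 over the two arms.
- Deaths needed for 70% power (Schoenfeld): 4 × (1.960 + 0.524)² / (ln 0.749)² = 295. Freedman's formula gives 299.
- Per group: 278 (Schoenfeld) or 282 (Freedman), against 280 stated. At 560 randomised, about 298 deaths and 70.4% power.

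The 560 is thus reproduced from 45% v 55%. The same sentence also speaks of a 5% difference, which does not match those inputs; that is a separate matter and is not used here.

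**Step 2: enrolment implied by a constant consent share.** Total needed = 560 / share.
- 10%: 5,600, i.e. 1,400 a year; 1,400/7,500 = 18.7%.
- 20%: 2,800, i.e. 700 a year; 9.3%.
- 50%: 1,120, i.e. 280 a year; 3.7%.

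The 7,500 covers all stages. The trial admits only pT1/2, pN1, R0 cases without capsule penetration or lymphangiosis.

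**Step 3: power if the share is 10%.** Total enrolment is assumed, as the article gives none. Power = Φ(½ × √deaths × |ln 0.749| − 1.960).

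| Total enrolled | Randomised | Deaths | Power | Share needed for 560 |
|---|---|---|---|---|
| 560 | 56 | 30 | 12% | 100% |
| 1,120 | 112 | 60 | 20% | 50% |
| 2,000 | 200 | 106 | 32% | 28% |
| 5,600 | 560 | 298 | 70% | 10% |

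The 10% threshold matches the target only if about 5,600 patients are enrolled.

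**The case against.** **Numbers are reviewed.** The yearly assessment looks at the randomised population, and too few leads to more sites. The consent share can then be read as a separate floor against the preference effect. This stands in part: a reader should not infer that counts are ignored. But the step has no figure and cannot stop the RCT.

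**The fallback is not lost.** A reader might infer that without an early stop the all-patient analysis is never reached, and that the RCT is locked in for nine years. The article does not support this. The second scenario depends on too few being randomised, not on an early stop, so it remains open at final analysis. Recruitment itself ends after 4 years, and observational patients follow the same protocol. What remains is that sufficient is unquantified, while the primary analysis is fixed on the randomised subjects.

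**The rule is not settled.** That 10% lets randomisation continue holds under the running text. Read literally, Table 1 would abort at 10%. The text also joins its two thresholds with *and*, which may mean that both must be missed. It is therefore tempting but unsafe to add that the cited 6.4% would need 8,750 enrolled (560/0.064), or 5% would need 11,200 (560/0.05). If each check stops the RCT on its own, a steady 5% or 6.4% misses the year-2 threshold and randomisation ends. Those totals arise only if both misses are required. On no reading is the rule tied to 560.

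**Infeasibility is inferred.** The article gives no count of eligible pN1 patients, no number of sites and no total enrolment, and consent may rise over time. This objection stands and limits the conclusion.

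**Conclusion.** The point holds in this form: the only numeric stop rule is a consent share with no link to the 560 randomised, so it does not test the condition the article sets for running the RCT. Under the running text, a steady 10% is compatible with power anywhere from about 12% to 32% if 560 to 2,000 are enrolled. The planned 70% is reached only at about 5,600 enrolled.

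This rests on the plan's 45% v 55% survival and 5% yearly dropout, uniform accrual, constant consent over four years, and an assumed range for total enrolment. The article does not show that 560 is unreachable. That is only a plausible inference from the words rare and few per centre, and from the 19% share of all-stage German cases. The firm finding is that passing the check says nothing about reaching the target. The change should be made.

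**What to change.** 1. Reconcile the running text with Table 1, and state whether missing one threshold is enough to stop randomisation or both must be missed.
2. At years 1 and 2, project the number randomised by the end of year 4 from the current rate and the sites opened, compare it with 560, and state the resulting power. For scale, an even pace is 560/4 = 140 a year; a projection that includes new sites need not be linear.
3. Have the sponsor set, with reasons and before outcome data are seen, the minimum projected number below which randomisation stops.
4. Use the same figure to define a sufficient number in the two analysis scenarios, and align it with the primary analysis named under Outcome measurements.
5. Keep the consent share as a descriptive measure of the preference effect.

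The cost is protocol wording; the counts are already needed for the planned assessments. The downside is that randomisation may stop earlier than under the share rule.

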## Conclusion

Under the constraints of a rare condition (pN1) and two substantially differing therapy arms, the practicality and obtainable evidence of a classical randomized study are challenged. The concept of a "Comprehensive Cohort Design" includes the option of a randomized study with an observational study as a backup if randomization of patients fails due to a strong preference effect.

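### Table 1 reverses the rule for stopping randomisation: both rows continue below 5% and 10% and abort otherwise, against the text that cites the table

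*Protocol article*

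**What the plan says.** The rule appears twice in the section Analysis of RCT and observational trial.

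- **Text.** The condition is consent to randomisation below 5% in year 1, joined by 'and' to the year 2 threshold and the consequence: "less than 10% within the second year, the RCT will be stopped and continued solely as an observational trial". The sentence refers the reader to Table 1.
- **Table 1, end of year 1.** "If fraction of randomized patients <5% of total count: ongoing recruitment, else abortion of randomization".
- **Table 1, end of year 2.** "If fraction of randomized patients <10% of total count: ongoing recruitment, else abortion of randomization".

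Three other statements show what the check is for:

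- The same section opens: "Carrying out this RCT is only justifiable if there is a realistic chance of enrolling enough patients to complete a meaningful statistical analysis".
- Randomization and Sample Size says that recruiting at least 280 patients per group into the observational study "will be pursued only in the unfortunate event that patient recruitment within the randomized trial fails".
- The Conclusion describes "an observational study as a backup if randomization of patients fails due to a strong preference effect".

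**The concern.** Below the threshold the text stops randomisation and the table carries on. At or above it the text carries on and the table aborts. Table 1 is the article's only schedule of these decision points, and the text points to it, so a reader who looks up what to do at a year end finds the wrong instruction.

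The rule decides whether there will be a randomised comparison. Under Outcome measurements, the primary analysis is by intention to treat in randomised patients. If too few are randomised, the plan changes to a covariate-adjusted analysis of everyone recruited. The trigger for that change should read one way only, and should be settled before consent rates are known.

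A smaller point concerns the logic. The text joins the two years with 'and', which can mean that both shares must fall short before anything stops. The table acts at each year end separately.

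**Working it through.** This is a comparison of rules; the plan states no figure to reproduce. Let f1 and f2 be the shares randomised at the end of years 1 and 2. The thresholds of 5% and 10% are the article's own.

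**Reading A: each threshold applies at its own look.** The text stops at year 1 if f1 < 5% and at year 2 if f2 < 10%. The table continues in exactly those cases and otherwise aborts. Each row taken as an instruction on its own:

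| Share randomised | Year 1: text / table | Year 2: text / table |
|---|---|---|
| 2%, 4.9% | stop / continue | stop / continue |
| 5%, 6.4%, 9.9% | continue / abort | stop / continue |
| 10%, 30%, 80% | continue / abort | continue / abort |

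The instructions are opposite in every cell.

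**Reading B: both conditions must be met before the text stops.** The text then stops only if f1 < 5% and f2 < 10%. Under the table, randomisation survives both looks only if f1 < 5% and f2 < 10%, which is the same condition with the opposite result:

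| f1 | f2 | Text, joint | Table 1 |
|---|---|---|---|
| < 5% | < 10% | stops after year 2 | continues |
| < 5% | ≥ 10% | continues | aborts at year 2 |
| ≥ 5% | < 10% | continues | aborted at year 1 |
| ≥ 5% | ≥ 10% | continues | aborted at year 1 |

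After both looks the outcomes are exact complements. At year 1 with f1 < 5%, however, both say continue, so in that case the conflict appears only at year 2.

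**Which direction fits the design.** The check exists to keep the RCT only if enough patients can be enrolled, and the observational cohort is the fallback if randomisation fails. A rule that aborts when the threshold is met, and continues when it is missed, contradicts both. The text's direction agrees with both.

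**Effect of reversing the rows.** With f1 ≥ 5% and f2 ≥ 10% as the conditions to continue, each row agrees with the text under reading A at every share listed above. It does not settle reading B. Two examples:

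- At 3% in year 1 and 12% in year 2, the joint text continues, while a corrected year 1 row would stop at year 1.
- At a constant 6.4%, the consent rate the Discussion reports for the breast cancer study it uses as its comparator, the joint text continues, the per-look text stops at year 2, and Table 1 as printed aborts at year 1.

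**The case against.** The best reply is that this is an evident slip in a schedule table. The sentence beside it states the rule in the sensible direction, the rest of the article supports that direction, and no investigator would abort randomisation because consent was good. Most of this stands. The intended direction can be recovered from the document, and no analysis, sample size or error rate depends on the error. It does not remove the need to correct the table, because the text cites it for this rule and both rows are wrong in the same way. Both rows are complete and identically worded, so damage in text extraction is an unlikely explanation.

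A second reply is that the 'and' is only loose wording. The section announces an assessment after each of the two years and gives one threshold for each, so two separate checks are the ordinary reading. That is fair, and the point is secondary. The joint reading is still open, and the stated purpose does not exclude it.

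Three stronger readings are tempting, and the article does not support them:

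- **Text and table disagree at every consent rate on any reading.** They do not. Under the joint reading they agree at year 1 below 5%. Under the per-look reading the instructions always oppose each other, yet the end state can coincide: at a constant 6.4% randomisation ends under both, at year 2 by the text and at year 1 by the table.
- **The 'and' leaves year 1 undetermined.** It does not. Read jointly, year 1 alone stops nothing, which is a definite instruction to continue. The open question is which reading is meant.
- **The trial is designed to abandon randomisation when consent is good.** Only the literal table says so, and everything else in the article points the other way.

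**Conclusion.** The point holds as a contradiction between text and table, and it should be corrected before the rule is used. Both rows of Table 1 state the go/no-go rule in the wrong direction. The conflict covers every consent rate if each threshold is applied at its own look. If the text's 'and' is read jointly, it covers every combination of the two shares once both looks are done, but not year 1 below 5%. The judgement that the table, and not the text, is at fault rests on the stated purpose of the check and on the fallback role of the observational cohort. It is an internal inconsistency and no criticism of the choice of 5% and 10%. Whether the conditions are separate or joint is a real but lesser ambiguity, which correcting the table alone would leave open.

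**What to change.** 1. Reverse both rows of Table 1. End of year 1: if at least 5% of the total count is randomised, recruitment continues, otherwise randomisation is aborted. End of year 2: the same with at least 10%.
2. Make the text follow the same logic. If the table's separate year-end checks are meant, replace the 'and' by wording such as: less than 5% at the end of year 1 or less than 10% at the end of year 2. If both shares must fall short before randomisation stops, say so in the text and in the table; the year 1 row then cannot abort randomisation by itself and has to be worded accordingly.

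The cost is two table rows and one sentence. Sample size, thresholds and analyses stay as they are.
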